### Sample size and power calculation

We plan to recruit at least 32 GPs across 4 regions. Based on Ferreira et al.’s trial findings, to detect a 15% difference between the control and intervention arm in CRC screening uptake, with an intra-cluster correlation (ICC) of 0.004 and a 25% attrition rate, a sample size of 1000 people eligible for screening is required [33]. This 15% difference is conservative. The ICC is based on previous studies similar to this trial. Each clinician will be expected to recruit approximately 32 patients, or as many eligible patients as possible if they cannot recruit 32, over the course of 1 year. On average, French GPs have about 300 eligible patients for CRC screening each year. Targeting 32 patients of about 300 represents just under 10%, which is achievable.

### Randomization

#### Sequence generation, type of randomization and allocation concealment

We will use an R script written by the trial statistician to perform the GP randomization. The random allocation sequence will be concealed until interventions are assigned. We will use block randomization to ensure a balanced allocation of each cluster (GP or GP office) in each region to the intervention and control arms. Participants recruited by GPs will therefore be a priori allocated to either the control or intervention arm by virtue of the GP that has recruited them. GPs will not be required to assess HL or deprivation levels (as these are not a inclusion or exclusion criteria) as the GP practice itself has already been identified as being located in a disadvantaged area.

#### Minimizing differential recruitment

To minimize differential recruitment, which can often occur in cluster randomized trials [48, 49], recruitment numbers in both arm of the trial will be routinely monitored at monthly team meetings. Once the target number of participants in each arm has been reached, recruitment will be stopped.

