### GP recruitment

To recruit GPs, we will first use a purposive sampling approach to include a balance of male and female GPs, practicing alone and in medical centers, in each region. GP work addresses will be coded against the EDI to establish if their practice covers a geographically disadvantaged area (EDI 4 or 5). GPs will be approached by email or telephone and given information about the trial. If this approach fails, we will transition to a convenience sampling approach, using contacts in our research network. Confirmation of participation will be by email and further contact details obtained. GPs will be randomly allocated to the control or intervention arm prior to the intervention training process, 2 months before patient recruitment begins. If a participating GP leaves their practice or decides to leave the trial, we will recruit another GP and assign him or her to the same arm.

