### Participation and recruitment procedures for trial entry

Within the 4 regional areas, clinical research assistants (CRAs) will work in collaboration with recruited GPs. Participants will be approached in primary care medical centers or at individual GPs’ offices by their doctor, a resident (“interne”), or another member of the medical center. Clinical staff will confirm eligibility (see Fig. 3) and obtain verbal consent. Once participants are recruited, CRAs will re-confirm verbal consent over the telephone and check whether they are able to complete the questionnaires alone or if they need assistance.

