### Blinding

Due to the nature of intervention delivery, it will not be possible to blind GPs to their allocation to either the control or intervention arm. At the individual level, patients invited to participate in the trial will likely be unaware that they are in the intervention or control arm. Furthermore, the CRAs collecting participants’ primary outcome data, assessing outcomes and conducting the analyses will not know to which group participants were allocated. The data analyst will also be blinded to arm allocation.

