### Statistical analysis

Initial examination of data will include descriptive statistics, frequency distributions, and histograms to identify outliers and missing data. The baseline data in each arm will be compared to ensure randomization was conducted successfully. We will use the Stata 16 software (Stata corp, US) to perform all analyses.

All participants will be asked to indicate at T1 if they have received the intervention to enable an intention-to-treat (ITT) and as-treated analysis. We will adopt a regression framework for all analyses as it allows seamless transition between basic analyses involving a single predictor and more complex analyses involving additional predictors (mediation variables, control covariates, time-trends, interaction terms or effect modifiers).

Further, the regression framework allows clustering of observations due to repeated measurements on patients across time, nesting of health professionals within sites, and patients within health professionals, to be accurately accounted for using mixed-effect regression models [53] or generalized estimating equations [54, 55].

### Analyses corresponding to aim 1

We will first perform separate analyses for each data collection period (T1 and T2) using linear and logistic regression models as appropriate for continuous (knowledge, patient activation, HL), and binary (screening intention, screening uptake, colonoscopy completed) outcomes respectively. The results will provide potentially valuable insights into how rapidly the intervention affects outcomes. Outcomes measured twice may also be analyzed using a longitudinal model. A secondary analysis that adds predictors for the number of patients seen by the healthcare professional in the intervention arms will examine whether there are physician learning effects. To gain insight into whether the intervention will be more effective according to the patient’s HL level and socioeconomic position, we will test the first order interaction between HL level/socioeconomic position and the intervention indicator variables. EPICES scores will also be used.

### Analyses corresponding to aim 2

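### Monitoring headcounts per arm controls how many patients are enrolled, not which ones, so it does not act on selective recruitment after allocation

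*Protocol article*

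**What the plan says.** The relevant statements are spread over several sections of the protocol article.

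- *GP recruitment*: "GPs will be randomly allocated to the control or intervention arm prior to the intervention training process, 2 months before patient recruitment begins".
- *Blinding*: "it will not be possible to blind GPs to their allocation to either the control or intervention arm".
- *Participation and recruitment procedures for trial entry*: patients are approached "by their doctor, a resident (“interne”), or another member of the medical center", and "Clinical staff will confirm eligibility (see Fig. 3) and obtain verbal consent". The clinical research assistant (CRA) comes in only after that, by telephone.
- *Sample size and power calculation*: "Each clinician will be expected to recruit approximately 32 patients, or as many eligible patients as possible if they cannot recruit 32", over one year, from roughly 300 eligible patients per GP.
- *Minimizing differential recruitment*: the section acknowledges that the problem is frequent in cluster trials. Its response is that "recruitment numbers in both arm of the trial will be routinely monitored at monthly team meetings", with enrolment closed once each arm has its target number.
- *Statistical analysis*: "The baseline data in each arm will be compared to ensure randomization was conducted successfully".

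Three other items bear on the point. Table 1 lists a count of eligible patients identified and enrolled. *Changes to intervention allocation* has CRAs record reasons for refusal. *Secondary outcome measures* includes previous screening tests, age and gender among the data collected from patients.

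**The concern.** Patients are not randomised. They take the arm of the GP who recruits them, at a time when the practice knows that arm. In such a design, the comparison is protected only if both arms enrol the same kind of patient from their lists. Each GP enrols a small fraction of those eligible, so there is room for the two arms to differ in whom they approach or persuade.

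The arms are also treated differently in ways that could affect this. Only intervention GPs are trained to discuss screening with patients of lower health literacy, and only they receive their own uptake rates at a booster session six months later. If training falls in the two months between allocation and first enrolment, the booster comes about 4 to 6 months into a 12-month recruitment period.

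The protocol names this threat and fixes a remedy for it. The remedy concerns numbers, while the threat concerns composition. If composition differs, the estimated effect on uptake is shifted by an amount the headcounts cannot reveal, and this cannot be fully repaired once enrolment has ended.

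**Working it through.** **Fraction enrolled.** The plan's own figure comes first: "Targeting 32 patients of about 300 represents just under 10%, which is achievable". The ratio is 32 / 300 = 10.7%, so slightly over a tenth. The slip is immaterial here. About nine in ten eligible patients per GP are not enrolled.

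**What the headcount rule constrains.** The plan is 32 GPs × 32 patients = 1024, or 512 per arm if equally split. The rule is met when both arms reach their number. Nothing in it depends on any patient characteristic, so it is met equally under no selection and under strong selection.

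**Possible size.** The article gives no figures on selection, so every input in this table is an assumption. Let s1 and s0 be the shares of previously screened patients among intervention and control enrolees, and let uA and uB be one-year uptake in previously screened and never-screened patients. With no true effect:

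spurious difference = (s1 − s0) × (uA − uB)

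| Case | s0 | s1 | uA | uB | Control uptake | Intervention uptake | Difference |
|---|---|---|---|---|---|---|---|
| Low | 40% | 45% | 50% | 20% | 32.0% | 33.5% | 0.05 × 0.30 = 1.5 points |
| Middle | 40% | 50% | 60% | 15% | 33.0% | 37.5% | 0.10 × 0.45 = 4.5 points |
| High | 40% | 60% | 70% | 15% | 37.0% | 48.0% | 0.20 × 0.55 = 11 points |

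Against the 15-point target these are 10%, 30% and 73%. The implied control uptakes lie near the national 30.5% given in *Background*. Exchanging s1 and s0 reverses the sign and leaves the size unchanged.

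**Effect on the test.** This is a second illustration, also assumed apart from the stated 30.5%, ICC 0.004, 25% attrition and N = 1000. Suppose 30% of the pool is ready to screen with 60% uptake. The rest then have (0.305 − 0.30 × 0.60) / 0.70 = 17.9%. Analysed patients per arm are 1000 × 0.75 / 2 = 375, or 375 / 16 = 23.4 per GP. The design effect is 1 + 22.4 × 0.004 = 1.09, giving about 344 effective patients per arm. If intervention practices enrol the ready group at k times its pool share, the difference is 0.30 × (k − 1) × (0.60 − 0.179). The chance of a significant result favouring the intervention (two-sided 5% test, no true effect) is:

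- k = 1: 0 points, 2.5%
- k = 1.25: 3.2 points, 14%
- k = 1.5: 6.3 points, 42%
- k = 2: 12.6 points, 93%

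Headcounts are the same in all four cases.

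**What adjustment can do.** In the middle case of the table, uptake within each stratum is the same in both arms (60% and 60%, 15% and 15%), so adjusting for previous screening removes the difference. If selection acts on willingness that is not measured, the difference remains.

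**The case against.** The strongest reply is that the plan holds more than headcounts. The eligible and enrolled counts, the refusal reasons, the baseline comparison by arm and the collected covariates can each show something about who was recruited. This stands: a reader might infer that counting heads is the trial's only safeguard, and that goes too far. It is the only measure offered against differential recruitment. The other records allow partial detection afterwards. None is tied to this purpose, refusal reasons miss patients who were never approached, and none prevents selection. Headcounts can also reveal unequal recruitment pace, but not unequal case-mix.

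A reader might also infer that GPs hand-pick their patients. The article does not say so. A resident or other staff member may make the approach, patients must attend and consent, and the order of approach is not given. An article may leave that detail to the full protocol. The criticism rests on the remedy the article does state.

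A third inference is that any baseline imbalance would mainly reflect recruitment. With about 16 clusters per arm, chance differences between GPs' patient populations are also a plausible source, and the article gives no means of separating the two.

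Finally, the covariates of the primary model are ordinary analysis-plan content, and *Statistical analysis* already allows control covariates. Their absence here is not a defect, and naming them is an improvement. The blinding of CRAs and the analyst is a real strength, but it protects outcome assessment and analysis, not enrolment.

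**Conclusion.** The point holds in this form: recruitment follows allocation, is done by practices that know their arm, and covers about 10.7% of the eligible list, while the stated measure against differential recruitment governs numbers only. It does not act on the bias it is meant to minimise.

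The size of any bias cannot be derived from the article. Under the assumed inputs it is about 1.5 to 11 points against a 15-point target, and that range follows from the inputs chosen. It shows that the bias could matter, not that it is likely.

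A reader might infer that a positive result would be a selection effect. The article does not support that. Trained practices might enrol more willing patients, which would inflate the effect, or more patients of lower health literacy who are harder to reach, which would mask one.

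The change should be made before enrolment starts or, failing that, for the remaining enrolment.

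**What to change.** 1. In *Minimizing differential recruitment*, have each practice approach consecutive eligible attenders until its target is met and keep a short log of those eligible, approached and refusing. Review the log by arm at the monthly meetings, together with the Table 1 counts and the refusal reasons the CRAs already record. A list of patients drawn before allocation is not proposed: listed patients would have to happen to attend, and GPs who replace those leaving would have no such list.
2. Adjust the primary uptake model for screening completed before the recruitment consultation, age and gender. All three are already collected. Because previous screening is asked at T1, one week after that consultation, the item should be worded to exclude tests done since then.
3. In *Statistical analysis*, read patient-level baseline imbalance as possibly due to chance between clusters or to recruitment after allocation, not simply as a check that randomisation worked.

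Item 1 costs some practice discretion over whom to approach and the time to keep a log. The review by arm should be kept from the CRAs and the analyst, who are to remain blinded. Items 2 and 3 are changes of wording to the analysis and to one questionnaire item. Adjustment does not remove selection on unmeasured willingness, so item 1 matters most.

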### Changes to intervention allocation

There are no established criteria for discontinuing or modifying the allocated intervention for study participants due to the low-risk nature of the trial. However, each CRA will be asked to record the reasons for patient refusal to participate/discontinuing at each stage of the study and to take field notes.

### Blinding

Due to the nature of intervention delivery, it will not be possible to blind GPs to their allocation to either the control or intervention arm. At the individual level, patients invited to participate in the trial will likely be unaware that they are in the intervention or control arm. Furthermore, the CRAs collecting participants’ primary outcome data, assessing outcomes and conducting the analyses will not know to which group participants were allocated. The data analyst will also be blinded to arm allocation.

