### Ethical approval, consent and recruitment strategies

The trial has received approval from the local research ethics committee, the Comité d’Ethique de la Recherche (CER) at the University of Toulouse III Paul Sabatier, France (ref 2021–349, dated 8th March 2021). Eligible participants will be asked to read a brief information sheet written in plain language or have a resident, mediator/patient navigator or other member of medical staff read the information out loud to them. This is particularly relevant since participants targeted by the trial are likely to have lower HL and lower textual literacy. According to the French health research classification, the ethics committee’s requirement for consent for this study requires participants’ verbal consent only or ‘non-opposition’ consent. Participants recruited by an intervention GP will be given a pictorial brochure about CRC screening and asked to watch a 3-min video on a tablet before exiting the primary care center/GP’s office. Participants recruited by a GP in the control arm will discuss the trial and CRC screening in their usual way.

One week after (T1), the CRA will call participants and offer to conduct a standardized telephone interview where the questions will be read out loud to them. Whenever possible, T1 data collection will be carried out in a single phone call. If the participant does not answer the first telephone call, the CRA will make three further attempts to contact them and leave up to three voice messages. CRAs will verify telephone contact details with the recruiting GP practices. Given participants are likely to have lower HL, this is the best strategy to maximize retention and minimize participant burden and missing data.

One year after (T2), CRAs will call participants for the follow-up assessment and offer to conduct a further standardized telephone interview. As with T1, attempts to verify contact details and to call the participant several times will be made.

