### Outcome measures

#### Primary outcome measure

The primary outcome measure is CRC screening uptake assessed 1 year after the initial recruitment consultation (T2) by self-report questionnaire (see Table 1). Each CRCDC, in collaboration with the health insurance body (CPAM) in each region, will also provide data on CRC screening uptake at 6 months (for feedback to GPs in the intervention arm) and 1-year post enrollment.

**Table 1 Tab1:** Outcome measures and data collection timepoints for patients

Outcome measures	Timepoints	
	(T1) One week after the primary care consultation where CRC screening is discussed	(T2) 1 year after the CRC screening consultation
Number of eligible patients identified and successfully enrolled	**X**	
Number of patients enrolled who receive the patient-facing intervention	**X**	
Discontinuation rate		**X**
CRC screening uptake (primary outcome) with self-report item		**X**
Screening intention (1 items)	**X**	
Knowledge of CRC screening (2 items)	**X**	**X**
Patient activation (13 items)	**X**	**X**
Health literacy (7 items)	**X**	
EPICES (11 items)	**X**	
SURE (4 items)	**X**	
Was the questionnaire completed alone? (1 item)	**X**	**X**
Demographics (9 items)	**X**	
**Total number of self-report items per timepoint**	**48**	**17**

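### The Blinding section says outcome assessors do not know the arm, but the T1 question on receiving the intervention can reveal it to the research assistants who make the outcome calls

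*Protocol article*

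**What the plan says.** **Blinding.** GPs cannot be blinded, and patients are described only as probably unaware of their arm. For the CRAs who collect the primary outcome the claim is unqualified: those "assessing outcomes and conducting the analyses will not know to which group participants were allocated".

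**Receipt question (Statistical analysis).** "All participants will be asked to indicate at T1 if they have received the intervention to enable an intention-to-treat (ITT) and as-treated analysis".

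**Who makes the calls (Ethical approval, consent and recruitment strategies).** "One week after (T1), the CRA will call participants and offer to conduct a standardized telephone interview", with the questions read out. Later, "One year after (T2), CRAs will call participants for the follow-up assessment".

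**Primary outcome (Primary outcome measure).** Screening uptake is "assessed 1 year after the initial recruitment consultation (T2) by self-report questionnaire". The regional screening centres (CRCDCs), with the insurer (CPAM), "will also provide data on CRC screening uptake at 6 months" and again at 1 year.

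**What marks the arm.** The section on consent and recruitment has the brochure and video given to patients of intervention GPs, while control GPs discuss screening as usual. The Randomization section fixes each patient's arm by the GP who recruited them.

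**Contact between CRAs and practices (Participation and recruitment procedures for trial entry).** "clinical research assistants (CRAs) will work in collaboration with recruited GPs". CRAs also check telephone details with the recruiting practices.

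**The concern.** The protocol states a safeguard and then describes a procedure that undermines it. A CRA who hears that a patient was given the brochure and shown the video has in effect been told the arm. Because allocation is by GP, that knowledge extends to the GP's other patients.

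The safeguard matters here because the primary outcome is self-reported, usually to an interviewer, and is open to prompting and to generous coding. GPs are unblinded and patients only presumed unaware, so blinding of the CRAs is the main stated protection for these outcomes. If it fails, assessor bias could enter the comparison, and the trial report would carry a blinding statement that the design does not support.

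**Working it through.** The protocol gives no figure on this point to reproduce. The check is who asks what, and when.

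1. **Does the T1 answer reveal the arm?** Only intervention GPs hand out the materials, so a yes points strongly to the intervention arm. A no fits a control patient, but also an intervention patient who did not receive or does not recall the materials. The disclosure is strong in one direction and weak in the other.

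2. **Does it reach beyond that patient?** The arm follows the GP. With about 32 patients expected per GP, one yes also informs on up to 32 − 1 = 31 others. CRAs can link a patient to a practice because they confirm contact details with it.

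3. **Do those who hear it collect outcomes?** CRAs conduct T1, which includes intention, knowledge, activation and decisional conflict (SURE). CRAs also conduct T2, which includes uptake, knowledge and activation. No text divides the staff between the two calls.

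4. **Does the order of questions protect the outcomes?** The Table 1 self-report items add up as stated:
   - T1: 1 + 2 + 13 + 7 + 11 + 4 + 1 + 9 = 48.
   - T2: 1 + 2 + 13 + 1 = 17.

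   The receipt question is not one of the 48. It appears only as a T1 count of patients who receive the patient-facing intervention, so its place in the call and its asker are not fixed. Even asked last at T1, it would inform later calls to the same GP's patients.

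5. **Do the planned analyses need the question?** Intention-to-treat needs only the GP's allocation. The as-treated analysis does need receipt data, but not data gathered by the outcome assessor.

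6. **Which outcomes are exposed?**
   - Exposed: self-reported uptake, intention, knowledge, activation, SURE.
   - Not exposed: colonoscopy completion (screening centres and insurer), the GP questionnaire (GPs' own report), and the CRCDC/CPAM uptake data.

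**Illustration only.** The inputs are 1024 enrolled, 25% attrition and ICC 0.004 from the protocol. It is assumed that true uptake is 30.5% in both arms (the national figure quoted in the Background) and that a share d of unscreened intervention patients is wrongly recorded as screened.

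- Analysed per arm: 1024 × 0.75 / 2 = 384. Analysed per GP: 32 × 0.75 = 24.
- Design effect: 1 + (24 − 1) × 0.004 = 1.092. Effective number per arm: 384 / 1.092 ≈ 352.
- False difference: d × (1 − 0.305).

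| d (assumed) | False difference | Chance of a significant result favouring the intervention (nominal 2.5%) |
|---|---|---|
| 2% | 1.4 points | about 6% |
| 5% | 3.5 points | about 17% |
| 10% | 7.0 points | about 49% |

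The documents give no value for d. The table shows how sensitive the primary test would be if misrecording occurred, and says nothing about how likely that is.

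**The case against.** The strongest reply is that the receipt sentence is passive and names no asker, the item is absent from the counted T1 items, and this is a condensed article whose full protocol may separate the roles. That much is fair: the text does not say that one individual calls a given patient both times. But the only T1 contact described is the CRA's call, and the blinding claim is made without qualification. The two statements do not fit together as printed.

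Several stronger readings are tempting and should not be drawn:

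- **That every outcome is compromised.** Three sources do not pass through CRAs, as listed in the working. Some patients may also complete the questionnaire alone, so not every answer is read out and coded by a CRA.
- **That a region is unblinded after a handful of calls.** With 32 / 4 = 8 GPs per region, a reader might infer that 8 answers suffice. That assumes one CRA per region who remembers each answer and an informative answer from every GP. The number of CRAs is not given, and a no is ambiguous.
- **That all T2 data will be collected unblinded.** This needs the same staff, or retained knowledge, a year later. The protocol neither states nor excludes it.
- **That the receipt question has no purpose.** The as-treated analysis needs the information.

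The CRCDC/CPAM uptake data at 1 year are a real mitigation. They do not rescue the blinding statement, because the primary outcome is defined by self-report.

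**Conclusion.** The point holds in a limited form. As written, the design does not deliver the assessor blinding that it claims for the interview-collected outcomes, including the self-reported primary outcome. This rests on three things the protocol does state: CRAs make both calls, all participants report receipt at T1, and the materials and the arm both follow the GP. It also rests on the absence of any described separation of callers or of any other asker for the receipt item.

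The contradiction itself is clear. Its consequence is not quantified: neither the probability nor the size of assessor bias can be derived from the documents, and the illustrative error rates depend wholly on assumed misrecording. It should be corrected before T1 interviews begin, but it does not invalidate the trial.

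**What to change.** **Preferred.** Take the receipt question out of the CRA interview. Have practice staff record delivery of the brochure and video when they are given, and keep that record from the CRAs who make outcome calls. The as-treated analysis keeps its data, and intention-to-treat uses the GP's allocation. The cost is a brief recording task per patient. The article describes no practice form for this, so a short one would have to be added.

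This closes the direct route only. CRAs would still work with unblinded GPs and contact their practices, so the Blinding section should say how the arm is kept out of those contacts.

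**If receipt must stay in the CRA call.** Change the Blinding section to say that outcome assessors are not reliably blinded, and report the 1-year CRCDC/CPAM uptake as a check on the self-reported primary outcome. Those data are already planned, so the cost is one additional analysis.

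**Not recommended.** Do not move the item to the end of the T2 call. One yes would still inform every later T2 call to that GP's patients, and patients would have to recall a brochure and a 3-minute video after a year.
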